**Figure 3 fig3:**
[figure not shown]
Overall protocol overview. After Study 1, patients who showed behavioral or EEG improvements following stimulation (either frontal or parietal) will be attributed to the corresponding group in Study 2. Patients who showed no improvement following either stimulation types will be randomized between the frontal and the parietal stimulation group in a 1:1 ratio. All patients will then be randomized between active and sham conditions in a 2:1 ratio. In Study 2, patients will be randomly assigned to either the active or the sham condition and will receive a longitudinal treatment protocol. The treatment phase will consist of stimulation sessions applied 20 min per day, 5 days a week during 4 weeks for a total of 20 stimulations sessions. Baseline (first day of stimulation, before the session) and post-treatment (last day of stimulation, after the session) assessments will include the CRS-R, 15 min resting state EEG and TMS-EEG to compute PCI. Follow-up measures (CRS-R and resting state EEG) will be collected at +1 and + 2 weeks following the end of the treatment phase. At 3 and 6 months following the end of the treatment phase, functional outcomes will be collected.

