### Procedure

#### Screening phase & enrollment

The study procedure will start at the earliest on the 28th day post-injury. All patients will be evaluated repeatedly (i.e., at least twice within 10 days prior to inclusion) with the CRS-R to confirm DoC diagnosis before enrollment. Existing CT or MRI-scans will be used to document structural lesions for neuronavigation-based targeting within 28 days before inclusion. Following screening phase, the legal surrogate of each eligible patient will be contacted for oral and written informed consent. After inclusion, every patient will first be enrolled in the crossover RCT protocol and will thus undergo four rTMS sessions. Based on the analysis of the patient’s best behavioral or electrophysiological response to either left DLPFC or left AG stimulation, the personalized protocol (4 weeks) will be started up to a week later.

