#### Randomized crossover trial

Within 10 days, all patients will undergo four rTMS sessions that will be administered in a randomized order and separated by a 72 h washout period: (i) one real stimulation over the left DLPFC, (ii) one real stimulation over the left AG, (iii) one sham stimulation over the left DLPFC, and (iv) one sham stimulation over the left AG. In this study, we chose to stimulate the left hemisphere because it tends to be more often targeted in non-invasive brain stimulation trials with DoC patients than the right hemisphere and because it was shown to have more promising results in other top-down electromagnetic-based techniques such as transcranial direct current stimulation (40). Randomization of the sequence of the four stimulation sessions will be stratified for gender, etiology, time post-injury, and diagnosis using computerized random number generator. Standardized behavioral assessments will be performed by experienced clinicians who will be blind to the nature of the sessions. The CRS-R will be performed before and after each stimulation session. Fifteen minutes of resting state high-density EEG will be performed directly before and after the stimulation (i.e., after the behavioral evaluation pre-stimulation and before the behavioral evaluation post-stimulation). Together with the EEG, electrooculogram (EOG) and electrocardiogram (ECG) will be recorded. See Figure 2 for the randomized crossover trial protocol.

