#### Personalized parallel trial

This trial will include three arms (i.e., DLPFC rTMS, AG rTMS and the sham-controlled condition). After a 1 week washout period following the randomized crossover study, the personalized parallel trial will be conducted. Based on their behavioral (primary) or electrophysiological (secondary) responses to either the left DLPFC or left AG treatment in the crossover RCT, patients will be assigned to one of two groups (i.e., DLPFC group if the patient was a responder to the DLPFC stimulation; AG group if the patient was a responder to the AG stimulation). If no behavioral response nor EEG change from the RCT could be obtained regarding the best stimulation hotspot or if the patient is a responder to both sites, the patient will be randomized into one of the two stimulation hotspots in a 1:1 ratio. Then, all patients will be randomized between the experimental condition and the sham condition following a 2:1 ratio by a randomized order generator. Only the investigator in charge of the randomization will be aware of the patients’ group allocation. The assigned intervention (i.e., active stimulation versus sham stimulation) will be concealed from the patient, the family, the care providers and all investigators involved in the patient’s assessment for the whole duration of the treatment phase. The evaluator will stay blind from the sequence as well as from the stimulation group during treatment and follow-up. Moreover, analyses will be conducted in a triple blind fashion (see *rTMS device* point for more information about blinding methods). All patients included in the trial will undergo 4 weeks (i.e., 20 working days) of stimulation. Behavioral effects will be assessed with the CRS-R at baseline and once a week during the 4 weeks stimulation protocol. Fifteen minutes of high-density EEG resting state will be performed right before and right after the first session as well as before and after the last session. Eventually, TMS-EEG acquisitions will be performed the first and last day of the 4 weeks protocol. As we will assess the effects following a single session (first stimulation session) and after 4 weeks of rTMS, we will be able to compare the effect of a single versus repeated sessions of stimulation. Figure 3 depicts an overview of the two studies.

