### Data analysis

#### Primary outcomes

For both crossover and longitudinal trials, primary analyses will focus on the detection of behavioral changes (i.e., enhanced behavioral total scores and/or changes in the level of consciousness as defined by the CRS-R) at the group level, comparing the sham interventions to the active interventions; and at the individual level, comparing post treatment to pre-treatment data. Along the same lines, analyses will also offer a comparison of the effects of frontal and parietal active rTMS on patients’ behavioral scores following one session of stimulation for the crossover RCT, and 4 weeks of stimulation for the longitudinal trial. Behavioral CRS-R total scores and subsequent index scores (50) will be defined as our primary outcome. Group treatment effects will be assessed with calculation of the difference between each group post-treatment and pre-treatment score means. Furthermore, we will identify clinical responders to (1) a single session of rTMS in the crossover trial and (2) the 4 weeks treatment protocol of the longitudinal trial as patients who will display new sign(s) of consciousness following treatment that was not present at baseline nor during the screening phase. In that context, further subgroup analyses will also be conducted along age, etiology, time since injury and diagnosis at inclusion.

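### The 4-week CRS-R contrast is stated against a single day-1 exam, although four earlier pre-randomisation exams are already collected and could sharpen it

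*Protocol article*

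**What the plan says.** For the 4-week trial, the Figure 3 legend fixes the two time points: "Baseline (first day of stimulation, before the session) and post-treatment (last day of stimulation, after the session) assessments will include the CRS-R". The section on the personalized parallel trial agrees: "Behavioral effects will be assessed with the CRS-R at baseline and once a week during the 4 weeks stimulation protocol".

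The primary outcomes section then defines the contrast: "Group treatment effects will be assessed with calculation of the difference between each group post-treatment and pre-treatment score means". The data analysis text computes Cohen's d from the same two time points, active against sham.

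The crossover that comes first yields more exams. There, "all patients will undergo four rTMS sessions that will be administered in a randomized order and separated by a 72 h washout period", and "The CRS-R will be performed before and after each stimulation session". Then: "After a 1 week washout period following the randomized crossover study, the personalized parallel trial will be conducted". The section on the personalized parallel trial places the 2:1 active/sham randomisation after the stimulation site has been assigned from the crossover results. All four pre-session exams therefore precede it.

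Outside the crossover itself, earlier exams enter the outcome analysis only through the responder definition, which requires a sign of consciousness not seen at baseline or during screening. The stated score contrast does not use the four pre-session exams.

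**The concern.** A single CRS-R measures a fluctuating patient with error. In a post-minus-pre contrast, the error of that one baseline exam passes into every patient's change. Adjusting for the day-1 score instead of subtracting it helps, but one noisy exam still represents the patient's underlying level imperfectly, and the unexplained part stays in the error term. Averaging several earlier exams gives a steadier picture of that level.

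The four pre-session exams could supply it without further assessments. They precede the active/sham randomisation, and every patient is scheduled for all four crossover conditions, so adjusting for them cannot favour either arm. At stake is the width of the confidence interval for active versus sham, the comparison named in the power calculation.

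**Working it through.** **Figures from the protocol.** The power calculation gives 74 evaluable patients and 90 recruited; both are taken as stated. The ratio is 2:1, so 74 splits into about 49 active and 25 sham. Four crossover sessions 72 h apart, followed by a one-week gap, put the pre-session exams at about days -16, -13, -10 and -7 relative to day 1 (day 0 in the model). The last treatment day of a four-week, five-day-a-week course is about day 26. The protocol states no CRS-R standard deviation, reliability or drift, so it has no variance figure to reproduce.

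**Assumed model.** Each exam has variance 1. A share r is true status and 1 - r is independent exam noise. True status correlates exp(-d/tau) between exams d days apart, with tau set by the assumed correlation c over the 26 days of treatment.

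**Formulas.** With m the mean of the four pre-session scores:
- Change score: 2 - 2rc
- Adjustment for day 1: 1 - (rc)²
- Adjustment for day 1 and m: 1 - b'S⁻¹b, where S is the covariance matrix of (day 1, m) and b holds their covariances with the post-treatment score

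**One case in full, r = 0.8 and c = 0.9.** Here rc = 0.72.
- Change score: 2 - 1.44 = 0.560.
- Day 1: 1 - 0.5184 = 0.482.
- Two covariates: var(m) = 0.838, cov(day 1, m) = 0.764, b = (0.720, 0.687). The weights S⁻¹b are 0.308 and 0.539. The explained part is 0.308 × 0.720 + 0.539 × 0.687 = 0.593, leaving 0.407.
- Cut beyond day-1 adjustment: 1 - 0.407/0.482 = 15%. Cut against the change score: 1 - 0.407/0.560 = 27%.

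**Residual variances at r = 0.8**

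| 26-day correlation c | Change score | Day 1 | Day 1 and m | Cut beyond day 1 | Cut vs change score |
|---|---|---|---|---|---|
| about 1 (0.999) | 0.402 | 0.361 | 0.240 | 34% | 40% |
| 0.9 | 0.560 | 0.482 | 0.407 | 15% | 27% |
| 0.8 | 0.720 | 0.590 | 0.545 | 8% | 24% |
| 0.7 | 0.880 | 0.686 | 0.660 | 4% | 25% |
| 0.5 | 1.200 | 0.840 | 0.832 | 1% | 31% |

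**Range over r = 0.7 to 0.9, cut beyond day 1:** about 30-37% for stable status, 10-17% at c = 0.9, 4-10% at 0.8, 2-5% at 0.7 and 0-2% at 0.5. Against the change score, the cut is about 17-41% over the whole grid.

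**Interval width.** It scales with the square root of the variance. At r = 0.8 and c = 0.9, √(0.407/0.482) = 0.92, so the interval narrows by 8%. At c = 0.8 it narrows by 4%, and at 0.7 by 2%.

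**Power at 49 versus 25, two-sided 0.05.** Take d as the effect divided by the day-1-adjusted residual SD. The noncentrality is d / [√(1 - cut) × √(1/49 + 1/25)], and √(1/49 + 1/25) = 0.246. For an assumed d of 0.5, power is 0.52 with no cut, 0.55 with an 8% cut, 0.59 with 15% and 0.70 with 34%. At d = 1.0, the two-equal-group equivalent of the protocol's f = 0.5, power is already 0.98.

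**The case against.** **This belongs to the analysis plan.** The strongest objection is that a condensed article need not list covariates, that a day-1 baseline is conventional, and that the Figure 3 legend gives assessment timing rather than a modelling rule. It is true that no passage forbids earlier scores, and an unseen analysis plan may add them. The article does, however, name the baseline exam and define the group effect as post minus pre, so the point is an improvement on a stated method. It does not correct an error.

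**The gain may be negligible.** This stands. Patients may enter soon after day 28 post-injury and may be recovering. The 30-37% figures need stable true status from the first crossover session to the end of treatment, about 42 days. The model also omits variation between patients in treatment response. Three of the four exams follow an earlier crossover session, so carryover or practice effects could add noise that it ignores.

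**Power is already ample at f = 0.5.** This is also true. The gain matters for effects smaller than the protocol assumes.

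**Stronger readings a reader might infer, which the documents do not support:**
- *The contrast is biased.* It is not. Active/sham allocation is randomised after all these exams.
- *The protocol contradicts itself, because screening requires repeated exams:* "All patients will be evaluated repeatedly (i.e., at least twice within 10 days prior to inclusion) with the CRS-R". That rule confirms the diagnosis at enrolment. It does not concern the score baseline.
- *Precision improves by about 40%.* That compares with the unadjusted change score under stable status. At r = 0.8 and c = 0.8, day-1 adjustment alone gives 18 of the 24 points (1 - 0.590/0.720).
- *Day 1 should be replaced by a mean of all five exams.* In calculations with persistent drift or patient-specific slopes, a change score from that pooled mean had 4% to 48% more variance than one from day 1 alone. Entering the exams jointly as covariates gave residual variance ratios of 0.66 to 1.00 relative to day-1 adjustment, so it never did worse.

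**Conclusion.** The point holds as a minor loss of precision. The stated score contrast rests on one day-1 exam, while four pre-randomisation exams that could reduce residual variance go unused in it. The benefit beyond day-1 adjustment runs from practically nothing to about a third of the variance, depending on how reliable a single CRS-R is and how far patients drift over a month. The protocol states neither. If the 26-day correlation of true status is 0.8 to 0.9, the cut is 4-17%. The validity of the comparison is not in question, and at the protocol's assumed effect the planned test would hardly change.

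**What to change.** State that the active-versus-sham comparison in the 4-week trial analyses the post-treatment CRS-R total score with two pre-randomisation covariates: the day-1 CRS-R, and the patient's mean of the available pre-session crossover CRS-Rs. Treat the index score in the same way. Keep day 1 as its own term and do not pool it with the earlier exams. If a crossover session was missed, use the mean of the remaining pre-session scores.

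The cost is one sentence of analysis wording, no new exams, and one degree of freedom beyond day-1 adjustment. With 74 evaluable patients, the residual degrees of freedom go from 74 - 3 = 71 to 70. That costs roughly 1/70, or 1.4%, of precision, so if patients drift strongly the net effect is about neutral.

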#### Assessment of adverse events & follow-up phase

Throughout both trials, all observed adverse events will be reported, described, and graded on a scale from 1 to 5 (1. mild, 2. moderate, 3. severe, 4. life-threatening, and 5. death referred to as severe adverse event). We will evaluate the proportion of patients who had adverse events and confront them with available adverse effect rates reported in the literature. Following the end of the 4 weeks treatment period, all patients will undergo behavioral (i.e., CRS-R) and neurophysiological (i.e., resting-state EEG) assessments 1 and 2 weeks after treatment to monitor immediate aftereffects. At 3 and 6 months timepoints following the end of the treatment, patient’s functional outcome will be collected. These evaluations will be carried out by means of structured phone interviews with the patient’s relatives/caregivers using the Disability Rating Scale (DRS) (41) and the Glasgow Outcome Scale-Extended (GOS-E) (42).

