As exploratory hypotheses, we also expect that MCS patients will be more likely to respond to the treatment than patients in UWS/VS. We also expect patients who received the active treatment to obtain better outcome at 3 and 6 months following the end of the intervention period compared to the sham group. No adverse event is expected in any of the three study arms.

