
The overall goal of this personalized trial is to improve the functional recovery at the clinical level. At the electrophysiological level, this study offers the opportunity to test different models of consciousness: anterior stimulation will allow to study the effect on consciousness recovery (32) according to the fronto-parietal mesocircuit model (28, 29) and the global neuronal workspace theory, suggesting that the hotspot of consciousness is located at the front of the brain (33, 34). Posterior stimulation – on the contrary – will allow for the testing of IIT claiming that the posterior part of the brain is the hotspot of consciousness (26, 27). We will use neurophysiological assessments as well as neurobehavioral exams to test the hypothesis that rTMS can modulate the neural network of the severely injured brain to promote the recovery of both consciousness at the clinical level, and functional thalamocortical network integrity at the neurobiological level. As such, this trial will bring direct evidence to challenge the above-mentioned models and will shed new light on the use of frontal and parietal rTMS as a therapeutic candidate to treat DoC.

A potential pitfall of this protocol might be the challenging timeframe of investigation. Indeed, full completion of the procedure of both trials should add-up to a total of 9 weeks. This is a particularly challenging feature since as we mentioned earlier, DoC patients are a very fragile population prone to complications and management issues. Safety precautions will be taken to avoid potential harm to the patients during the study, especially during the rTMS stimulation sessions, and to allow patients to complete the protocol.

This protocol stands as an important milestone in the development of new patient-tailored therapeutic options in the field of DoC. Our findings could usher in a new era of research for a challenging patient population in desperate need of medical solutions.

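### The only adverse-event comparison the article states is with published rates; the trial's own randomised sham should be the main comparator

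*Protocol article*

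**What the plan says.** In the Protocol article, the section Assessment of adverse events & follow-up phase covers collection fully: "Throughout both trials, all observed adverse events will be reported, described, and graded on a scale from 1 to 5". On analysis it has one sentence: the investigators will work out what share of patients had events and "confront them with available adverse effect rates reported in the literature". The Abstract adds only that events are recorded during treatment.

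Both parts of the study contain a sham control:

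- **Crossover** (Randomized crossover trial): "all patients will undergo four rTMS sessions that will be administered in a randomized order and separated by a 72 h washout period". Two of the four sessions are active and two are sham, one of each at each site.
- **Parallel trial** (Personalized parallel trial): "all patients will be randomized between the experimental condition and the sham condition following a 2:1 ratio by a randomized order generator". Allocation is concealed from the patient, family, care providers and assessors during treatment.

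The comparison of sham with active in the Primary outcomes section is written for CRS-R results: "primary analyses will focus on the detection of behavioral changes". Adverse events are not mentioned there or under Secondary outcomes.

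Two other statements bear on the point. Study objectives and hypotheses says "No adverse event is expected in any of the three study arms". The Discussion says "DoC patients are a very fragile population prone to complications and management issues".

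**The concern.** Patients this ill will have medical events during a procedure that the Discussion puts at 9 weeks in all, whether or not they are stimulated. The safety question is therefore whether events are more frequent with active stimulation than without it. A published rate answers that only if it carries the same background risk, ascertainment and length of observation, and nothing in the article secures this. The article itself says, under Therapeutic options in DoC, that earlier rTMS protocols in these patients differ in site, intensity and number of sessions. It also chooses to keep patients with lesions at the stimulated site.

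If the stated comparison were the one reported, a high background could be attributed to rTMS, or a real excess could be passed over because it falls within a published range. The reading would depend on which published rate was chosen.

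The unit of analysis adds a second difficulty. The sentence counts patients, and events are collected across both trials. Every patient receives active stimulation in the crossover, including those later randomised to sham. A proportion of patients taken over the whole study therefore contains no one unexposed.

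**Working it through.** The article gives no adverse-event rate, precision or power, so there is no stated figure to reproduce. The event rates below are assumptions, used only to show scale.

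**1. What the stated analysis can identify.** Suppose 30% of active patients have an event in the parallel trial. Two situations give that figure:

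| | Background | rTMS excess | Active | Sham | All 90 patients |
|---|---|---|---|---|---|
| A | 30% | 0 points | 30% | 30% | 30% |
| B | 10% | 20 points | 30% | 10% | (60 × 0.30 + 30 × 0.10)/90 = 23.3% |

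The active rate is the same in A and B. Within the trial, the sham rate is what tells them apart. If the proportion were pooled over arms, the excess in B would also be diluted.

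**2. Numbers available for a sham comparison.**

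- Parallel trial: 90 recruited at 2:1 gives 90 × 2/3 = 60 active and 90 × 1/3 = 30 sham. With the 74 patients that the Power calculation section says are needed, the split is about 49 and 25.
- Crossover: 90 × 2 = 180 active and 90 × 2 = 180 sham sessions, before dropout, in the same patients.

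**3. Precision of the risk difference in the parallel trial.** With the same event rate p in both arms, the 95% half-width is 1.96 × √[p(1 − p)(1/n_active + 1/n_sham)].

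| Assumed p | 60 active, 30 sham | 49 active, 25 sham |
|---|---|---|
| 10% | 1.96 × √(0.09 × 0.0500) = 0.131 | 1.96 × √(0.09 × 0.0604) = 0.145 |
| 30% | 1.96 × √(0.21 × 0.0500) = 0.201 | 1.96 × √(0.21 × 0.0604) = 0.221 |

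**4. Power, Fisher's exact test, two-sided 0.05.**

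| Sham v active (assumed) | 60 active, 30 sham | 49 active, 25 sham |
|---|---|---|
| 5% v 20% | 40% | 37% |
| 10% v 30% | 56% | 44% |
| 20% v 40% | 43% | 37% |
| 10% v 40% | 87% | 78% |

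**5. Rare events.** With no events in n patients, the one-sided 95% upper bound is 1 − 0.05^(1/n): 4.9% for 0/60 active and 9.5% for 0/30 sham. For an event such as seizure, the sham arm alone says little.

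**6. Exposure.** In the crossover, active and sham can be separated only if each event is tied to the session it followed. In the parallel trial every patient enters having had the same number of active and sham sessions, so the randomised contrast stays fair even though the sham arm is not free of earlier active stimulation.

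**The case against.** The strongest reply is that two sentences in a journal article are being read as a complete safety analysis. The text does not say that literature rates are the only comparator, that arms will be pooled, or that sham data will be set aside. Tables of events by arm are often left to a full protocol or SAP, and neither is shown. This stands as a limit on what can be claimed. It does not remove the point, because the article is not merely silent: it names an external comparator and omits the randomised one.

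A reader might infer that the trial has no means of telling whether rTMS causes events, or that the sham controls go unused. The documents do not support either. Events are collected in both conditions, under blinding, so the data allow a sham comparison. The limitation lies in the analysis as written.

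A reader might also see a contradiction between the expectation of no adverse events and the description of a fragile population. That goes too far. The first is an expectation placed among exploratory hypotheses and can be read as meaning events due to stimulation, while the second is about complications in general. The wording is loose, and it is a minor side point.

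Nor can it be asserted that the published rates come from other populations or devices, since the article does not say which literature is meant. They may come from rTMS studies in the same kind of patient. They would still lack a randomised contrast with this trial's patients.

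Finally, the half-widths measure the precision of the proposed comparison, not the harm of the present text, and power for 15- to 20-point excesses is only about 40% to 56% even without dropout. This is correct. It argues for an estimate with an interval, and for keeping literature rates alongside it for rare events.

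**Conclusion.** The point holds in a limited form. The article states one adverse-event comparison, with published rates, and names none with its own randomised sham. That analysis, as written, cannot separate background events from an rTMS excess, and a per-patient proportion over both trials has no unexposed group.

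The bias of the literature comparison cannot be quantified from the document. What can be sized is the alternative: a 95% half-width of about 13 points at a 10% event rate and 20 points at 30% with 60 active and 30 sham patients, or about 14 and 22 points with 49 and 25. These figures rest on assumed event rates, equal in the two arms, and on a normal approximation. The comparison would show a large excess and would not reliably detect a modest or rare one. No efficacy conclusion is affected.

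**What to change.** Make active versus sham the main safety comparison and say so in the section on adverse events.

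- **Parallel trial:** give the proportion of patients with events by randomised arm, with the active-minus-sham risk difference and its 95% CI. Present it as an estimate and not as a test that could establish safety.
- **Crossover:** tie each event to the session it followed, and compare active with sham sessions within patient. Use a window of the same length after every session, within the 72 h gap, so that the last session is not observed for longer than the others.
- **Literature rates:** keep them as context, mainly for rare events such as seizure, and state which sources will be used.
- **Side point:** reword the expectation of no adverse events so that it is clear whether it means events due to stimulation.

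The cost is one table and one or two sentences. No new data are needed, provided that the case report form dates each event closely enough to place it after a given session.
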